## Abstract

*Background.* Internet-based complex interventions aiming to promote weight loss and optimize healthy behaviors have attracted much attention. However, evidence for effect is lacking. Obesity is a growing problem, resulting in an increasing demand for cost efficient weight loss programs suitable for use on a large scale, for example, as part of standard primary care. In a previous pilot project by Brandt et al. (2011) without a control group, we examined the effects of online dietician counseling and found an average weight loss of 7.0 kg (95% CI: 4.6 to 9.3 kg) after 20 months. *Aims and Methods.* To analyze the effects of a complex intervention using trained dieticians in a general practice setting combined with internet-based interactive and personalized weight management support compared with conventional advice with a noninteractive internet support as placebo treatment in 340 overweight patients during a 2-year period. Primary endpoints are weight loss and lowering of cholesterol (LDL). We will also explore patients' sociodemographics and use of the intervention as well as the health professionals' views and perceptions of the intervention (their role and the advice and support that they provide). *Perspective.* The project will generate knowledge on the cost-effectiveness of a complex internet-based intervention in a general practice setting and on barriers and acceptability among professionals and patients.

## 1. Introduction

Obesity is a growing problem and more than 30% of the European population is obese with a body mass index (BMI) >30 kg/m^2^. Weight loss decreases the risk of obesity related complications such as type 2 diabetes, cardiovascular events, and joint and musculoskeletal diseases as well as improves fertility and reduces the risk of spontaneous abortion. The expected economic implications of weight loss among the obese are reduced sick leave and substantially lower demand on health support.

Controlling dietary intake and increasing physical activity through behavioral change programs in a face-to-face setting have previously been demonstrated to produce significant weight loss [1]. However, implementing such programs into general practice has shown to be difficult due to a number of barriers [2]. Face-to-face consultations are time consuming both for the health professionals and for the patient, and many general practitioners do not offer sufficiently extensive behavioral support to fully achieve the potential effect [2]. In order to achieve a major behavioral change, information must be so clearly relevant for the patient that they cannot easily choose to ignore it [3]. When face-to-face consultations are used on their own (without extensive follow-up measures), long-term effects compared to controls are difficult to detect [4]. Furthermore, in Denmark access to professional dieticians is limited due to the costs of the public health care system.

New interactive media can be used in weight management [5–12]. The effects in primary care have been variable [12], but using the internet seems to be more cost-effective, even when the magnitude of the effect is not affected [13]. Personal individual advice can be delivered either synchronously or asynchronously. By delivering the advice asynchronously important communication can be managed at a very low cost due to the fact that digital communication is stored and parts of it can be reused for many patients in templates or articles [14]. Matched peer support through online communities where patients can meet other patients in a similar situation as themselves can offer important support, and established relations between patients and health professionals seem to be important drivers for successful outcomes [6, 12, 15].

In a recent prospective pilot study without a control group we investigated the effect of a medium intensive online dietician advice combined with a community using the existing commercial online weight loss management program “SlankeDoktor” [16]. We found a mean weight loss from baseline of 7.0 kg (95% CI : 4.6–9.3 kg) after a mean maintenance period of 20 months among 21 patients with an initial BMI of 36.4 kg/m^2^ [17].

## 2. Aims

To evaluate the impact of a complex intervention using face-to-face contact with trained dieticians combined with interactive online support and follow-up, as compared with usual care, on BMI and metabolic risk factors.To explore the feasibility of the intervention by assessing patients' sociodemographic characteristics and use of the different services in the intervention in relation to their weight loss.To explore the usability and applicability of the intervention in relation to the health professionals' view and perceptions of the intervention (their role and the advice and the support that they provide).

## 3. Materials and Methods

A multicentered two-arm randomized controlled trial.

### 3.1. Patients

The study will recruit 340 patients registered in general practices within 4–6 medical centers, representing a population of approximately 40,000 citizens. The medical centers will be invited to participate and consecutively included. They will be both rural and city centers and have between 2 and 10 doctors working at each center. Doctors and practice staff will hand out information material about the study. Patients are included consecutively until there is a total number of 340 patients randomized to either intervention group or control group, respectively. The practice staff will register everyone agreeing to participate. We expect to include initial 500 patients before randomization as our experience from the pilot study is that 25% of those who agree to participate do not fill out the online registration form required to be randomized [17] (Figure 1).

### 3.2. Inclusion Criteria

The patient has a BMI ≥ 30 kg/m^2^.The patient is 18−70 years old.The patient provides informed consent.The patient has home access to the internet.The patient is not pregnant.The patient has no serious or life threatening disease.The patient has no weight loss >3 kg within the last 2 months.

### 3.3. Exclusion Criteria

The patient fails to complete the initial questionnaire online.The patient becomes pregnant during the study.The patient experiences serious or life threatening disease during the study.The patient moves to another GP practice not participating in the study.The patient has a serious eating disorder or develops one during the study (e.g., rapid weight changes).

Patients will be invited consecutively by doctors and practice staff. The first information is received at the medical center, ensuring full confidentiality. Patients who receive information concerning the study from doctors or practice staff and who agree to participate are registered and scheduled for an appointment with a nurse. The patients will be able to bring a friend or relative in accordance with ethical guidelines for biomedical experiments with humans. An appointment with a nurse is scheduled within 7–14 days after the information; thus the patient has sufficient time to reflect on the decision to participate. The nurse obtains the approved informed consent and proceeds with weighing and measuring the patient. The patient is then instructed to use a web link to a standard quality of life questionnaire including SF12 and other relevant questions from the webpage www.praksis.sundhedsdoktor.dk. Patients are randomized immediately after the questionnaire is filled out, using an automated computer algorithm. This procedure ensures that dropouts can be recorded as well as certain characteristics for the patients who choose to drop out.

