### 3.6. Data

Answers to the standard quality of life questionnaire are collected at the medical center by a nurse at inclusion at 6 months and at 24 months.

Patient characteristics will be entered at the start. Patient height, waist and hip circumference, blood lipids, Hba1c, and weight are measured at inclusion after 6 months and 24 months.

The blood samples will be collected by the bioanalyst in the practice in accordance with guidelines for the handling of blood measurements in Danish general practice and analyzed at the certified laboratory at Odense University Hospital.

Data will be continuously added to a database by the patient, nurse, and dietician.

Number of logins, number of entrances in the different sections of the site, and user patterns will be collected from the database at 6 months and again at 24 months. Dieticians, nurses, doctors, and other health professionals from the medical center will be interviewed about the intervention in relation to their work, their role, their perception of the treatment offered, and the strength and weaknesses seen from their perspective in accordance with the MAST models organizational dimension (Table 1) [18].

In the case of exclusion before the end of the trial, for example, by pregnancy, the patient will if feasible be asked to complete a final questionnaire and have objective parameters measured in order to provide data for an “intention to treat” analysis. The medical centers will be responsible for this. Data and answers to questionnaires will be collected at 6 months and 24 months by independent observers that will assign each patient to a number to mask the identity for the analysts.

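### Events after randomisation are listed as exclusion criteria with only an exit measurement, so the procedure does not ensure the intention-to-treat analysis it names

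*Protocol article*

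**What the plan says.** Section 3.3 of the protocol article (Exclusion Criteria) contains four items that can take effect during the trial: "The patient becomes pregnant during the study"; "The patient experiences serious or life threatening disease during the study"; "The patient moves to another GP practice not participating in the study"; and "The patient has a serious eating disorder or develops one during the study (e.g., rapid weight changes"). The last item covers both an existing and a newly developing disorder. Its only example is a change in weight, given without a threshold, a time window or an assessor.

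The same section fixes the time of randomisation: "Patients are randomized immediately after the questionnaire is filled out, using an automated computer algorithm". The remaining item, failure to complete the online questionnaire, therefore acts before randomisation and raises no difficulty.

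Section 3.6 (Data) schedules weight, waist and blood measurements at inclusion, 6 months and 24 months. For anyone excluded earlier, with pregnancy as the example, "the patient will if feasible be asked to complete a final questionnaire and have objective parameters measured", and the stated purpose is "in order to provide data for an “intention to treat” analysis". Nothing says that such patients are measured again at 24 months. Section 4 (Statistics) makes change in body weight and waist circumference the primary objective.

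**The concern.** An intention-to-treat comparison needs the planned outcome on every randomised patient, or as near to that as can be managed, whatever happens after allocation. Here an event during the trial ends participation, and the only safeguard is a single measurement at the time of the event, if it can be obtained. The 24-month value is then never collected, and no analysis plan can recover it.

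This matters most where the event may depend on the arm:

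- **Eating disorder.** The only sign named is a change in the primary outcome variable. A programme that works should produce more large changes.
- **Pregnancy and serious disease.** The Introduction says that weight loss improves fertility and lowers the risk of diabetes and cardiovascular events, so both could differ between arms if the intervention succeeds.
- **Detection.** Intervention patients keep daily records and have weekly online dietician contact for six months, then monthly (section 3.4). Controls see a nurse or doctor about once a month and have a non-interactive site (section 3.5). The Discussion says that the number of face-to-face consultations is the same in both arms, so the difference lies in the online records and contact.

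Pregnancy also affects the value itself: weight and waist at that exit reflect the pregnancy as well as the programme.

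**Working it through.** **Step 1. The plan's own figure, to obtain an SD.** Section 4 gives 142 per group for a 2.5 kg difference at 90% power. It does not give the SD, alpha or sidedness. Assuming two-sided 5%:

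SD = 2.5 × √(142/2) / (1.960 + 1.282) = 6.50 kg.

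I use 6.5 kg as an assumption. The confidence interval reported for the pilot (4.6 to 9.3 kg, 21 patients) implies less: 2.35 × √21 / 2.086 = 5.16 with a t quantile, or 2.35 × √21 / 1.960 = 5.49 with a normal one. A smaller SD would put fewer patients beyond the thresholds below and reduce the bias.

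**Step 2. Expected means, from section 4 (midpoints).** At 6 months: −6 kg (from 5–7) against −2.5 kg (from 2–3), a difference of 3.5 kg. At 24 months: −4 kg (from 3–5) against 0, a difference of 4.0 kg. A 6-month exit weight thus overstates the 24-month loss by 6 − 4 = 2 kg in the intervention arm and by 2.5 − 0 = 2.5 kg in the control arm.

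**Step 3. Weight-triggered exits (illustration).** Assumptions not in the documents: 6- and 24-month changes are bivariate normal with SD 6.5 and correlation ρ of 0.5 or 0.7; a patient exits at 6 months if the change in either direction exceeds c = 12, 15 or 20 kg. For 6-month mean m6 and 24-month mean m24:

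a = (−c − m6)/6.5, b = (c − m6)/6.5, P = Φ(b) − Φ(a), k = [φ(a) − φ(b)]/P

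- mean 24-month change of those kept = m24 + ρ × 6.5 × k
- mean with exit values carried = P × (mean of those kept) + (1 − P) × (mean exit value)

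Worked case, c = 12 and ρ = 0.5:

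- Intervention: a = −0.923, b = 2.769, excluded 18.1%, k = 0.3075; kept mean = −4 + 3.25 × 0.3075 = −3.00.
- Control: a = −1.462, b = 2.231, excluded 8.5%, k = 0.1136; kept mean = 3.25 × 0.1136 = +0.37.
- Patients lost: difference 3.00 + 0.37 = 3.37 kg.
- Exit values carried (mean exit values −15.06 and −10.47): intervention 0.819 × (−3.00) + 0.181 × (−15.06) = −5.18; control 0.915 × 0.37 + 0.085 × (−10.47) = −0.55; difference 4.63 kg.

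| c (kg) | Excluded, intervention / control | Lost, ρ = 0.5 | Lost, ρ = 0.7 | Carried, ρ = 0.5 | Carried, ρ = 0.7 |
|---|---|---|---|---|---|
| 12 | 18.1% / 8.5% | 3.37 | 3.12 | 4.63 | 4.44 |
| 15 | 8.4% / 3.1% | 3.64 | 3.50 | 4.41 | 4.28 |
| 20 | 1.6% / 0.4% | 3.90 | 3.86 | 4.12 | 4.08 |

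Against 4.0 kg with everyone measured, the range is about 3.1–3.9 kg if the patients are lost and 4.1–4.6 kg if exit values are carried.

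**Step 4. Balanced exits unrelated to weight.** If a fraction p of each arm leaves near 6 months and the exit value is carried, the difference is 4(1 − p) + 3.5p. For p = 5%, 10% and 15% this is 3.98, 3.95 and 3.93 kg, which is negligible.

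**The case against.** The strongest reply is that this is largely a labelling matter in a condensed article. The items read like withdrawal reasons, the intention-to-treat aim is declared, and the exit measurement shows that the authors want to keep these patients in the analysis. How exit, missing and pregnancy-affected values enter a model is ordinary SAP content. That last point stands, and the absence of a missing-data method is not part of this finding. What remains is a rule about what gets collected: an exit measurement where feasible, and no stated follow-up to 24 months.

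Three stronger readings are tempting and not supported:

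- *Patients are removed on the outcome itself.* The criterion is a serious eating disorder, and rapid weight change is only an example of a sign. It overlaps with the primary outcome variable but is not the outcome, and it covers gain as well as loss.
- *The exit value replaces the 24-month value.* No section says so. It is a natural inference from the stated purpose, but using the value at its own date in a longitudinal model is equally compatible with section 3.6.
- *Excluded patients leave the analysis, so it is not intention-to-treat.* No section says that either. The text supports only that the procedure does not ensure such an analysis.

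The illustration can also fairly be attacked. The thresholds are invented, and treating every patient beyond one as having an eating disorder is extreme. It shows that the bias can go either way; it does not forecast its size.

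**Conclusion.** The concern holds in limited form. Events after randomisation are written as exclusion criteria; one is judged partly on the primary outcome variable and is easier to notice in the intervention arm; and the plan secures only an exit value where feasible. Followed as written, it can leave 24-month outcomes uncollected for reasons that may depend on the arm.

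The documents determine neither the size nor the direction of the bias. The ranges in the working rest on the section 4 midpoints and on an assumed SD, correlations and thresholds. They move below 4.0 kg if patients are lost and above it if exit values are carried, and they stay close to 4.0 kg if exits are balanced and unrelated to weight. The case for correction rests on the missing 24-month data and does not depend on any one of these figures.

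**What to change.** 1. Divide section 3.3 into eligibility at entry and events during the study.
2. State that such an event may end the allocated programme, which is a clinical decision left to the investigators, but does not end outcome measurement or remove the patient or their data from the analysis. The eating-disorder item and its example can stay as a clinical matter; this point asks for no change to it.
3. State that all randomised patients are analysed in their assigned arm.
4. Keep the 6- and 24-month measurements for everyone who consents, including those who move practice.
5. Use an exit measurement only at its actual date, never as the 24-month value.
6. Treat weight, waist and lipids measured during pregnancy as missing, and handle them in a longitudinal model or by multiple imputation.

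The cost is modest but not nil. A few more patients must be followed. Movers are by definition outside the participating centers, which section 3.6 makes responsible for the measurements at exclusion, so an arrangement for measuring them is needed. Some more values will be imputed.

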### 3.4. Intervention Group

Patients randomized to the intervention group receive a login to the website “http://www.praksis.sundhedsdoktor.dk/” as well as a consultation with a certified clinical dietician within 2 weeks. The website has been developed over a 12-year period with focus groups, usability testing, and user involvement from both patients and health care professionals. At “http://www.praksis.sundhedsdoktor.dk/” the patients fill in a daily diet record as well as their comments, concerns, and questions to the dietician, who will have access to all patient profiles. Patients can monitor and follow their weight loss progress at the website. They have access to a community where they can discuss and chat with other patients and share weight loss experiences as well as give advice and support to each other. Patients receive subsequent 15–30 min consultations with the dietician by appointment at the start and up to every 6 weeks for 6 months to a total of 5 (Figure 2). The certified clinical dieticians also provide individual asynchronous online consultation [14] according to their patients' needs and based on information supplied via the website. The online consultations are weekly during the first 6 months and after that they are monthly. The dietician generates a daily caloric reduction plan of approximately 2400–3200 KJ based on the patients' starting weight, diet record, and physical activity. The dietary advice will be as standardized as possible. In collaboration with the patient goals for obesogenic behavior changes are set up like “eat breakfast every day,” “no late night meal or snack,” and so forth that follow the dietary guidelines given at “http://www.praksis.sundhedsdoktor.dk/” and The Danish Health and Medicine Authority (Sundhedsstyrelsen). A personal trainer evaluates the exercise by monitoring information given by the patients and encourages them to increase their physical activity to a level of at least. Patients will be encouraged to increase their physical activity to a level with at least 30 min daily. Three times a week the physical activity is suggested to be of moderate to high intensity.

### 3.5. Control Group

Patients randomized to the control group will receive usual treatment through the medical center, which consists of approximately monthly face-to-face consultations with a nurse or doctor. Additionally they will receive a “placebo treatment” in the form of a login to a website that looks like http://www.praksis.sundhedsdoktor.dk/, but contains only general non-interactive and non-personalized dietary and exercise advice (e.g. “all about diet” from the National Food Agency (Fødevarestyrelsen)), but with neither dietician consultations nor community membership.

### 3.6. Data

Answers to the standard quality of life questionnaire are collected at the medical center by a nurse at inclusion at 6 months and at 24 months.

Patient characteristics will be entered at the start. Patient height, waist and hip circumference, blood lipids, Hba1c, and weight are measured at inclusion after 6 months and 24 months.

The blood samples will be collected by the bioanalyst in the practice in accordance with guidelines for the handling of blood measurements in Danish general practice and analyzed at the certified laboratory at Odense University Hospital.

Data will be continuously added to a database by the patient, nurse, and dietician.

Number of logins, number of entrances in the different sections of the site, and user patterns will be collected from the database at 6 months and again at 24 months. Dieticians, nurses, doctors, and other health professionals from the medical center will be interviewed about the intervention in relation to their work, their role, their perception of the treatment offered, and the strength and weaknesses seen from their perspective in accordance with the MAST models organizational dimension (Table 1) [18].

In the case of exclusion before the end of the trial, for example, by pregnancy, the patient will if feasible be asked to complete a final questionnaire and have objective parameters measured in order to provide data for an “intention to treat” analysis. The medical centers will be responsible for this. Data and answers to questionnaires will be collected at 6 months and 24 months by independent observers that will assign each patient to a number to mask the identity for the analysts.

## 4. Statistics

The primary objective of this study is measurement of changes in body weight and waist circumference. Weight loss in the intervention group and control group will be analyzed using appropriate statistical procedures. A weight loss of 5–7 kg in the study group and 2-3 kg in the control group is expected after 6 months of treatment. After 2 years we expect the control group to return to the starting weight, while the study group is expected to maintain a weight loss of 3–5 kg. A power calculation, based on standard deviations observed in a previous pilot project [17], shows that to detect a difference in weight loss of 2.5 kg with a power of 90% requires 142 patients per group. 170 patients will be randomized to each group to allow for dropouts. Secondary outcome such as logins, web site activity, and user patterns will be analyzed in relation to the different quartiles. The most active quartile will be compared to the least active quartile in relation to weight loss, and other measured parameters. If the difference in sustained weight loss after 2 years is greater than 2.5 kg, the planned total of 340 patients will allow analyses of interactions between treatment, gender, age and obesity level. Due to this, the randomization will be stratified by gender, while potential effects of and interactions with other recorded characteristics such as smoking, age and obesity level will be analyzed as continuous or discrete variables as appropriate.

All data will be blinded and the randomization code and identity of the patients will not be revealed to the data manager before analyses are completed. Data will be analyzed by statistical experts. After the study, all data will be made accessible on the internet in anonymized form to allow full peer scrutiny and facilitate secondary research.

